##### 6.3.1.2. Analysis of secondary outcomes

All analysis of the secondary endpoints will follow the intention-to-treat (ITT) principle. It will be based on the FAS with missing data of the primary outcome imputed as described in the section “Missing data” (section 6.4).

The continuous secondary endpoints (outcomes operation time, anaesthesia time, volumetry of side ventricles, and Evan’s Index) will be assessed using linear regression models, the binary endpoints (optimal catheter placement, complications, mortality and revision surgery) will be assessed using logistic regression, and the number of puncture attempts will be assessed using a poisson regression model.

All estimates will be reported with 95% CI. IF numbers allow explanatory variables will be BMI, underlying diagnosis, experience surgeon and the use of an old burr hole.

In case the outcome variable is not normally distributed or model assumptions are violated, data will be transformed or a different model, depending on the distribution of the data, chosen.

Deviation from the original statistical plan:

If substantial deviations of the analysis as outlined in these sections are needed for whatever reason, the protocol will be amended. All deviations of the analysis from the protocol or from the detailed analysis plan will be listed and justified in a separate section of the final statistical report.

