#### 6.4. Missing data

Missing baseline and outcome data will be summarized by study arm. As outlined above, the primary analyses will be the intent-to-treat population. In the case of missing data or drop-outs, we may adjust for further baseline variables which are associated with missing outcome data or we consider multiple imputation. Both, baseline patient characteristics and outcome variables will be considered for multiple imputations. Variables with more than 50% missing values will not be used for the imputation model. Categorical variables with a frequency of 5% or less in one category will also be omitted. Continuous variables will be imputed using linear regression and binary variables using logistic regression. We will construct and analyze 20 imputed data sets and combine results using Rubin's rules. Diagnostic checks, including model convergence and comparing observed versus imputed distributions, will be performed to ensure the quality of imputations.

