## 9.2. Assessments of outcomes

### 9.2.1. Assessment of primary outcome

Primary outcome (surgical intervention time) will be recorded for every operation by anaesthesiology, as it is standard in our department. This time spans the time spent in the OR by the neurosurgeon, beginning with any intervention on the patient (e.g. positioning, head clamping) and ends when the neurosurgical part of the operation is finished, so it consists of the preparation time, and the operation time of the neurosurgical part of the operation together. To minimize bias, the visceral surgery part of the operation (laparoscopically assisted insertion of the peritoneal catheter intraperitoneally) will not be included into this time interval.

[figure not shown]

**Figure 1: Composition of the surgical intervention time (preparation time plus operation time neurosurgical part), plus additional five minutes in the stereotactic navigation group.**

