### **11.5 Handling of missing data and drop-outs**

Missing baseline and outcome data will be summarized by study arm. As outlined above, the primary analyses will be the intent-to-treat population. In the case of missing data or drop-outs, we may adjust for further baseline variables which are associated with missing outcome data (which is analogous to performing multiple imputation in the case of a single endpoint). We may consider multiple imputation as sensitivity analyses if necessary.

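### The SAP's missing-data rule for the secondary analyses imputes the primary outcome, and its primary analysis uses an imputation that the protocol keeps for sensitivity analysis

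*Combined protocol and SAP*

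**What the plan says.** **Primary analysis.** SAP 6.3.1 bases it on the full analysis set (FAS) with missing surgical times imputed under section 6.4. The covariates are BMI, diagnosis, surgeon experience and use of an old burr hole.

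**Secondary analyses.** SAP 6.3.1.2 uses the same sentence: "It will be based on the FAS with missing data of the primary outcome imputed as described in the section" on missing data. The secondary models have the same four covariates, if numbers allow.

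**Method.** SAP 6.4 is conditional at first: "we may adjust for further baseline variables which are associated with missing outcome data", "or we consider multiple imputation". It then says "Both, baseline patient characteristics and outcome variables will be considered for multiple imputations", and ends firmly: "We will construct and analyze 20 imputed data sets and combine results using Rubin's rules".

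**Protocol.** Section 11.5 offers the same covariate adjustment but gives imputation a lesser role: "We may consider multiple imputation as sensitivity analyses if necessary". Section 9.2.1 says that the surgical time "will be recorded for every operation by anaesthesiology".

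**Declared changes.** SAP 7 reports no change from the protocol.

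**Analysis set.** SAP 4.4 limits the FAS to randomised patients who completed follow-up. Protocol 11.4.1 includes everyone randomised.

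The SAP appears twice in the combined file, with the same text on all these points.

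**The concern.** A missing-data rule should say what happens to missing values of the outcome being analysed. The rule in SAP 6.3.1.2 names a different outcome. An imputed surgical time fills no gap in catheter position, ventricular volume, Evans' index or revision, and it is not a covariate in those models.

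Missing values are more likely in the secondary outcomes than in the primary one. The surgical time is captured on the operation day, while the CT measures and revision run to 6 months. Missingness there could also depend on the outcome. Protocol 7.4 withdraws patients whose shunt dysfunction leads to revision on the same side and location, and protocol 9.2.5 plans no further assessments for patients who stop early.

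For the primary outcome, pre-specification is at stake. The protocol and SAP give imputation different roles, and SAP 6.4 sets no trigger for choosing between adjustment and imputation. That choice could therefore be made after the data are seen, and SAP 7 tells the reader that the two documents agree.

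**Working it through.** **1. Role of imputation, side by side**

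| Place | Primary outcome | Secondary outcomes |
|---|---|---|
| Protocol 11.5 | Optional adjustment; imputation only as sensitivity analysis | Same text, no separate rule |
| SAP 6.3.1 | Imputed, under 6.4 | Not covered |
| SAP 6.3.1.2 | Named as the outcome to impute | Not named |
| SAP 6.4 | Adjustment or imputation | Considered for imputation |
| SAP 7 | No change declared | No change declared |

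The SAP differs from the protocol on the primary outcome. It is also unclear within itself, since 6.3.1 is firm and 6.4 is optional.

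**2. Does an imputed surgical time enter any secondary model?** The modelled outcomes are operation time, anaesthesia time, ventricular volume, Evans' index, optimal placement, complications, mortality, revision and puncture attempts. The covariates are the four listed above. Surgical intervention time is in neither list. It could serve as an auxiliary variable, for operation time for example, but the SAP does not say so.

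**3. Size for the primary outcome**

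Inputs from protocol 11.2: target 15 min, SD 28.65 min, alpha 5%, power 80%, drop-out 1%, non-adherence 5%, 68 per group (136 in total). Two-sided testing is from SAP 4.2.

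The plan's own figure first:

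- n per group = 2 × [28.65 × (1.960 + 0.842) / 15]² = 57.3, rounded up to 58. This matches the stated 58.
- Inflation: 58 / (0.99 × 0.95²) = 64.9, so 65 per group and 130 in total, as in SAP 2.3. The protocol's total of 136 adds 6 patients.

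Patients affected, if every planned drop-out lacked a time: 0.01 × 136 = 1.36, or about 1 to 2.

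Shift in the mean difference when k imputed times in one arm are each wrong by one SD, k × 28.65 / 68:

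- k = 1: 0.42 min, which is 2.8% of 15 min.
- k = 2: 0.84 min, which is 5.6% of 15 min.

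If 1% of times are lost instead, power at 68 per group falls from 86.3% to 85.9%.

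**4. Size for the secondary outcomes.** The documents give no rate of missing CT or 6-month data. Under an assumed range of 5% to 15%, 0.05 × 136 = 6.8 and 0.15 × 136 = 20.4. So about 7 to 20 patients per outcome would have a missing value with no settled rule. This is a count under an assumption; it is not an estimate of bias.

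**5. Which patients are there to impute for?** Read literally, SAP 4.4 removes drop-outs before any imputation, including operated patients whose surgical time was recorded. Protocol 11.4.1 keeps them. The FAS definition therefore decides how much there is to impute.

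**The case against.** The strongest defence is that the phrase in SAP 6.3.1.2 is a copying slip and harms nothing. The sentence points to 6.4, which covers outcome variables generally and gives a method for binary variables, although the primary outcome is continuous. On the primary side, 6.4 still permits the protocol's covariate adjustment. Protocol 11.5 regards that adjustment as analogous to imputation for a single endpoint, and protocol 11.4.2 leaves details to the SAP. All of this supports calling the primary effect small. It does not settle which method is primary, and *considered* is not a rule for the secondary outcomes.

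A reader might infer more than the documents support:

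- **That a missing time means no operation, so an imputed time is meaningless.** This is inferred from routine recording at every operation. The per-protocol definition lists completed surgery and an available primary measurement as separate conditions, so an operated patient may lack a time. Withdrawal of consent is another possible route.
- **That secondary outcomes will be analysed on observed cases only.** SAP 6.4 leaves their imputation open; it is undecided, not excluded.
- **That CT or revision values will be imputed after death.** SAP 2.3 counts deaths as drop-outs, and SAP 4.4 removes drop-outs from the FAS. The risk arises only under the protocol's FAS, where nothing rules it out.
- **That the faulty sentence also governs shunt dysfunction.** That is a safety endpoint under SAP 6.5 and is not among the outcomes of 6.3.1.2.
- **That the primary analysis should be confined to operated patients.** Neither document defines such a set, and adopting one would itself be a protocol change.

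**Conclusion.** The point holds as a fault of specification. SAP 6.3.1.2 names the wrong outcome and so states no working rule for missing secondary outcomes. SAP 6.3.1 gives imputation a role that protocol 11.5 does not, and SAP 7 leaves this undeclared.

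The primary estimate is little affected: about 0.4 to 0.8 min against 15 min. That figure assumes 68 per arm, one or two missing times in the same arm, and errors of one SD in the same direction. The 1% behind it is the planned drop-out by deaths, used here only for scale, because a patient who dies after surgery would normally have a recorded time. The size of any secondary effect cannot be determined from the documents. The case for correction rests on fixing the analysis before the data are seen, at almost no cost.

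**What to change.** 1. **SAP 6.3.1.2:** replace the reference to the primary outcome with *the outcome concerned*. State that the randomised arm is in the imputation model and that outcomes not defined after death are not imputed.
2. **SAP 6.3.1 and 6.4:** make the primary analysis the recorded times by allocated arm with the pre-specified covariates. Report, per arm, how many patients have no time and why. Keep multiple imputation as the sensitivity analysis of protocol 11.5. If the sponsor prefers imputation in the primary analysis, list and justify that in SAP 7.
3. **SAP 4.4:** align the FAS with protocol 11.4.1 (all randomised), or declare the difference.
4. Make the same corrections in the second copy of the SAP.

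The cost is SAP wording and one sensitivity run, with no new data and no additional patients.

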### **4.3 Secondary Objectives**

Further we are interested in special aspects of safety and feasibility of the navigation methods in direct comparison to each other, such as positioning of the catheter (optimal/not optimal, grade I to IV, safety), rate of VPS dysfunction and revision surgery (safety), number of ventricular puncture attempts that have been made (safety and feasibility), operation and anaesthesia times (feasibility), and any complications and morbidity (safety), as well as death (safety).

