### 5.2 Secondary Outcomes

- Secondary outcomes are:
  - Operation time in minutes (time in minutes from “Schnitt” to “Naht”)
  - Anaesthesia time in minutes (time in minutes from “Beginn Anästhesie” to “Ende Anästhesie”)
  - Number of puncture attempts
  - Catheter placement (optimal vs. not optimal): Optimal catheter placement has been defined as free-floating within the CSF without touching the ventricle wall or septum pellucidum, and the tip of the catheter located at the foramen of Monro showing an optimal length of the catheter. Catheters that did not fulfill all criteria have been defined as not optimal placed. Positioning of catheters will be further graded according to Yim et al. into grades I to IV (grade I: catheter terminates in the ipsilateral frontal horn, grade II: catheter terminates in contralateral frontal horn, grade III: catheter terminates in non-targeted CSF spaces, grade IV: catheter terminates intraparenchymally).
  - Volumetry of side ventricles pre- and postoperatively in cm^3 (number and relative change)
  - Evan’s Index pre- and postoperatively (number and relative change)
  - Complications (infection, bleeding, complications ass. with navigation method), mortality
  - Revision surgery (yes/no) and reason for revision

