### 5.4 Safety Outcomes

- The positioning of the catheter
- Number of ventricle puncture attempts
- VPS dysfunction, the revision rate
- perioperative complications (bleeding, infection), complications due to head clamp
- death, coma (<1% expected)

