### 9.2.2. Assessment of secondary outcomes

Operation time and anesthesia time in minutes: these times will be assessed at the operation day by anaesthesiology

Number of puncture attempts: this will be assessed at the operation day by the operating surgeon

Catheter placement (optimal vs. not optimal): between the 2nd and 5th postoperative day a CT scan will be made and VPS positioning will be assessed. Optimal catheter placement is defined as free-floating within the CSF without touching the ventricle wall or septum pellucidum, and the tip of the catheter located at the foramen of Monro showing an optimal length of the catheter. Catheters that did not fulfil all criteria have been defined as not optimal placed. Positioning of catheters will be further graded according to Yim et al. into grades I to IV (grade I: catheter terminates in the ipsilateral frontal horn, grade II: catheter terminates in contralateral frontal horn, grade III: catheter terminates in non-targeted CSF spaces, grade IV: catheter terminates intraparenchymally).

The cCT scan will be repeated during second follow-up after 6 months. This outcome will be assessed by partially blinded neuroradiologists.

Volumetry of side ventricles pre- and postoperatively in cm^3 (number and relative change): This will be assessed on the pre- and postoperative CT scans by partially blinded neuroradiologists.

Evan's Index pre- and postoperatively (number and relative change): This will be assessed on the pre- and postoperative CT scans by partially blinded neuroradiologists.

Complications (infection, bleeding, complications ass. with navigation method), mortality: rate and detail of complications will be assessed directly postoperative during the whole hospitalisation time and during the 1st and 2nd follow-up by the study nurse, the same accounts for mortality (including the reason for death if known).

Revision surgery (yes/no) and reason for revision: the rate of revision surgery as well as the indication for revision will be reported by the study nurse.

VPS dysfunction: the rate of VPS dysfunction will be assessed directly postoperative during the whole hospitalisation time, and during the 1st and 2nd follow-up by the study nurse.

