#### **11.4.3 Secondary Analyses**

The secondary outcomes will be analysed using linear regression models (for the outcomes operation time, anaesthesia time, volumetry of side ventricles, and Evan's Index), logistic regression models (for the outcomes optimal catheter placement, complications, mortality and revision surgery), or a Poisson regression model (for the outcome number of puncture attempts).

All estimates will be reported with 95% CI. All models will be adjusted for the most important risk factors. We will compare each endpoint between the intervention and control arms. Further details will be provided in the statistical analysis plan.

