#### **11.4.5 Safety analysis**

Safety will be assessed via a rigorous and detailed examination of adverse events between the treatment group and the control group. Safety endpoints will be assessed using the FAS.

Safety endpoints are the following events: positioning of the catheter, number of ventricle puncture attempts, VPS dysfunction, revision rate, perioperative complications (bleeding, infection), complications due to head clamp, death, and coma.

Binary safety endpoints will be compared as number of events between the two groups (US and stereotactic navigation) using a logistic regression. To compare the number of ventricle puncture attempts per patient between the treatment and control arm we will use a Poisson regression model.

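### SAP 6.5 replaces the protocol's logistic regression of VPS dysfunction by randomised arm with an as-treated listing and an optional comparison, while SAP 7 declares no change

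*Combined protocol and SAP*

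**What the plan says.** **Protocol**

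- Section 4.3 names the rate of VPS dysfunction among the secondary objectives, next to revision surgery, and tags it as safety.
- Section 9.2.2, on assessing secondary outcomes, gives it its own entry: "VPS dysfunction: the rate of VPS dysfunction will be assessed directly postoperative during the whole hospitalisation time". The entry goes on to cover both follow-up visits, the second at 6 months.
- Section 5.4 lists "VPS dysfunction, the revision rate" among the safety outcomes.
- Section 11.4.5 includes dysfunction in its list of safety endpoints and states: "Binary safety endpoints will be compared as number of events between the two groups (US and stereotactic navigation) using a logistic regression". On the population it says: "Safety endpoints will be assessed using the FAS". Section 11.4.1 defines that set as everyone randomised, analysed by allocation.
- Sections 5.2 and 11.4.3 do not contain dysfunction. The nearest item in 5.2 is "Revision surgery (yes/no) and reason for revision".

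**SAP**

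- Section 6.1 repeats the protocol 5.2 list without dysfunction. In 6.3.1.2, "the binary endpoints (optimal catheter placement, complications, mortality and revision surgery) will be assessed using logistic regression".
- Section 6.5 keeps dysfunction by name as a safety endpoint. It provides for a listing by treatment actually received, and for a frequency comparison only if adverse events turn out to be many. It gives no threshold and no model.
- Section 4.4 limits the full analysis set (FAS) to randomised patients with completed follow-up.
- Section 7 declares no changes from the protocol.

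**The concern.** The protocol motivates navigated placement partly by the link between catheter position and shunt malfunction (3.1), and it cites fewer proximal failures with navigation (3.4). One would expect that consequence to have an effect estimate by randomised arm. The protocol promises one in 11.4.5. The SAP, which governs what will be run, does not.

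Two things are at stake. A stated secondary objective could end with descriptive tables and a listing only. If a comparison is made, the SAP points to grouping by treatment received, which gives up the protection of randomisation for this endpoint. A reader relying on SAP 7 would not know that either change had been made.

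**Working it through.** **Step 1. The two safety analyses side by side.**

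| Feature | Protocol 11.4.5 with 11.4.1 | SAP 6.5 with 4.4 |
|---|---|---|
| Is a comparison made? | Yes, without condition | Only if adverse events are numerous; no threshold |
| Method | Logistic regression | None named |
| Grouping | Randomised allocation | Treatment actually received, for the listing; the comparison that follows names no other grouping |
| Patients | All randomised | Randomised with completed follow-up |

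The SAP differs in all four rows, and SAP 7 declares none of these differences. The condition is also unclear. Protocol 9.2.4.1 confines study adverse events to death and navigation-related complications, whereas 10.3.1 is broad, so dysfunction may or may not count toward it.

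**Step 2. Does another SAP analysis cover dysfunction?**

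- *Secondary regressions (6.3.1.2):* no. The four binary endpoints do not include it, and protocol 11.4.3 has the same four.
- *Complications:* not in general. The visit records in protocol 9.3 collect complications other than dysfunction. Infection could enter here, but non-infectious obstruction, dislocation or disconnection has no clear place.
- *Revision surgery:* only when the patient is reoperated. The treating physician knows the arm (protocol 6.2.2). Even this route may lose patients: protocol 7.4 withdraws those revised for dysfunction on the same side and location, and the SAP's FAS requires completed follow-up.
- *Descriptive tables (4.1):* these give frequencies by intervention group, without an effect estimate or interval.

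Dysfunction that is not reoperated therefore has no guaranteed estimate by randomised arm.

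**Step 3. Why the grouping matters.** Protocol 8.3 allows a preoperative switch from ultrasound to stereotactic navigation for very small ventricles. It also allows an intraoperative switch the other way after unsuccessful stereotactic placement, for example with distorted anatomy. Those who switch are selected on anatomy, so an as-treated comparison moves selected, difficult cases between groups.

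**Step 4. Size.** The plan gives no dysfunction rate, sample size or power for this endpoint, so there is no figure to reproduce. Inputs: 136 patients, 68 per arm (protocol 11.2). Assumptions: dysfunction by 6 months of 5% to 30%, equal in both arms, with 10% to 30% of events not reoperated.

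- Events = 136 × p
- Not reoperated = events × 0.10 to events × 0.30
- Half-width of the 95% CI for the risk difference = 1.96 × √(2p(1−p)/68)

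| p (assumed) | Events, both arms | Not reoperated | Half-width, points |
|---|---|---|---|
| 5% | 6.8 | 0.7 to 2.0 | 7.3 |
| 10% | 13.6 | 1.4 to 4.1 | 10.1 |
| 20% | 27.2 | 2.7 to 8.2 | 13.4 |
| 30% | 40.8 | 4.1 to 12.2 | 15.4 |

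For p = 10%: 1.96 × √(2 × 0.10 × 0.90/68) = 1.96 × 0.0515 = 0.101. The normal approximation is rough at 5%, with about 3.4 events per arm. With the SAP's total of 130, the counts shrink by the factor 130/136.

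**The case against.** A reader might infer that the SAP dropped dysfunction from the secondary outcomes and their regressions. The documents do not support that. Protocol 5.2 and 11.4.3 never contained it, and SAP 6.1 and 6.3.1.2 match them. That gap lies inside the protocol: 4.3 and 9.2.2 against 5.2 and 11.4.3.

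Nor has dysfunction vanished from the SAP. Section 6.5 names it, 4.1 would tabulate it by group, and 2.4 says all endpoints are analysed for superiority. What is missing is a committed, model-based estimate by randomised arm.

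It is also tempting to say that differences in willingness to reoperate will be read as differences in dysfunction. No section treats revision as a stand-in for dysfunction; revision is a separate endpoint with recorded reasons, including bleeding and infection.

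Other points carry some weight:

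- As-treated grouping is not foreign to the protocol: 7.4 mentions an as-treated analysis after surgeon non-adherence. SAP 4.4 also says that all analyses follow allocation, so one could argue that any comparison under 6.5 would too. But 6.5 is the specific rule, and nothing says that 4.4 overrides it.
- The replacement affects every binary safety endpoint without its own regression, such as coma and head-clamp complications. Dysfunction stands out because it is also a secondary objective.
- Dysfunction is assessed by the study nurse, with no stated blinding and no diagnostic criteria. A regression does not cure that.
- The estimate would be imprecise. But SAP 4.2 asks for effect measures with intervals, and mortality is already in the logistic list although protocol 5.4 expects death and coma in under 1%.

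**Conclusion.** The point holds as a discrepancy between protocol 11.4.5 and SAP 6.5 that SAP 7 does not declare, together with an inconsistency inside the protocol over whether dysfunction is a secondary outcome. This rests on the text alone. If the SAP is followed as written, dysfunction that is not reoperated has no guaranteed effect estimate by randomised arm, and a comparison under 6.5, read with its own listing rule, would be as-treated.

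The size rests entirely on assumed rates: about 1 to 12 events across both arms, with the low end negligible. The documents do not show that a bias will occur, or in which direction. The matter should be corrected before the data are analysed. It does not touch the primary outcome.

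**What to change.** 1. In SAP 6.5, restore the protocol 11.4.5 logistic regression for VPS dysfunction (yes/no, surgery to Visit 6) by randomised arm, with a 95% CI and whatever the number of adverse events. Alternatively, add dysfunction to SAP 6.1 and 6.3.1.2 and align protocol 5.2 and 11.4.3 with 4.3 and 9.2.2.
2. Keep the as-treated listing as a supplement.
3. Use the protocol 11.4.1 FAS (all randomised) for this endpoint. Count dysfunction that occurred before any withdrawal under protocol 7.4 as an event, rather than excluding patients without completed follow-up. State how patients who leave without dysfunction before Visit 6 are handled.
4. Amend SAP 7 to declare and justify any difference that remains, including for the other binary safety endpoints in 6.5.

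The cost is one more regression and a few lines of text. Dysfunction is already recorded at Visits 2 to 6, with details of cause from Visit 3, so no new data are needed. The downside is a wide interval, which should be reported as an estimate and not read as evidence of equivalence.

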## 2.3. Sample size

The sample size was estimated with the aim of showing a surgical intervention time reduction of 15 minutes (min) in the intervention arm compared to the control arm. The significance level was chosen to be 5%, while the power was chosen to be  $(1-\beta) = 80\%$ .

Based on unpublished data from a pilot study assessing the surgical intervention time in patients undergoing VPS placement using US navigation, we calculated a mean surgical intervention time of 63 min with a standard deviation (SD) of 28.65 min. Because of the additional steps involved using stereotactically navigated surgery, we assume an increased surgical intervention time in those patients.

We then conservatively selected a scenario with a relatively modest difference between groups. This resulted in 58 patients with VPS placement surgery per group. Anticipating a 1% drop-out by deaths and a surgeons' non-adherence rate (change from control to treatment arm) of 5%, a total sample size of 130 patients (65 per group) was required.

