## 4.2. Confidence intervals and p-values

The statistical testing will be two-sided with a significance level of 5%. All tests will be accompanied by an effect measure with a 95% confidence interval (95% CI).

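### Plain Poisson regression is planned for puncture attempts, a count that in effect starts at one; its standard error is unlikely to be right, and no robust or quasi-Poisson variance is specified in advance

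*Combined protocol and SAP*

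**What the plan says.** Three sections plan the same model. SAP 6.3.1.2 says "the number of puncture attempts will be assessed using a poisson regression model". Protocol 11.4.3 lists "a Poisson regression model (for the outcome number of puncture attempts" and leaves details to the SAP. Protocol 11.4.5, on safety, says "To compare the number of ventricle puncture attempts per patient between the treatment and control arm we will use a Poisson regression model". None of them names a robust, quasi-Poisson or truncated variant. Estimates are to carry 95% confidence intervals, and SAP 4.2 sets two-sided tests at 5%.

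On how the count arises, protocol 9.2.2 has only "Number of puncture attempts: this will be assessed at the operation day by the operating surgeon". No mean, variance, first-attempt share or power is given for this outcome.

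SAP 6.3.1.2 has a fallback: if the outcome is not normally distributed "or model assumptions are violated, data will be transformed or a different model, depending on the distribution of the data, chosen". Protocol 11.4.5 has no such sentence. Protocol 11.4.6 requires substantial deviations to be handled by amendment and all deviations to be listed and justified, but it names no alternative model.

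**The concern.** Poisson regression fixes the variance at the mean. A count that cannot be zero does not follow a Poisson distribution: with a mean of 1.2, for instance, a Poisson model would put exp(−1.2) = 30% of patients at zero attempts. If most patients have exactly one attempt and few have many, the real variance lies well below the mean. The model-based standard error is then too large and the test too conservative.

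Puncture attempts is a secondary outcome (protocol 5.2, SAP 6.1) and a safety outcome (protocol 5.4 and 11.4.5, SAP 6.5). Protocol 4.3 counts it under both safety and feasibility. For a safety comparison an over-wide interval is the unhelpful direction, because a real excess of attempts in one arm could be reported as no clear difference.

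**Working it through.** **Inputs.** From the documents: Poisson model, two-sided 5%, and 65 patients per arm (SAP 2.3) or 68 (protocol 11.2). The planned 58 evaluable per arm reproduces for the primary endpoint: 2 × (1.960 + 0.842)² × 28.65² / 15² = 57.3, rounded up to 58; then 58 / 0.99 / 0.95² = 64.9, so 65. There is no stated figure for puncture attempts to reproduce. The distributions below are assumptions.

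**Formulas.** For two arms of size n with means m1, m2 and variances v1, v2, on the log mean ratio:
- Poisson SE = √(1/(n·m1) + 1/(n·m2))
- true SE = √(v1/(n·m1²) + v2/(n·m2²))

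With equal arms the ratio of the two is √(mean/variance).

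**Worked case.** With 85/10/5% at 1/2/3 attempts, the mean is 0.85 + 0.20 + 0.15 = 1.20 and the variance is (0.85 + 0.40 + 0.45) − 1.20² = 0.26. The factor is √(1.20/0.26) = 2.15.

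**Range.** Rejection rates with no difference come from 20,000 simulated unadjusted trials at 65 per arm:

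| Assumed % at 1/2/3/… attempts | Mean | Variance | CI too wide by | Type I, Poisson | Type I, robust |
|---|---|---|---|---|---|
| 90/8/2 | 1.12 | 0.146 | 2.77 | 0.00% | 5.7% |
| 85/10/5 | 1.20 | 0.260 | 2.15 | 0.01% | 6.0% |
| 80/15/5 | 1.25 | 0.288 | 2.09 | 0.01% | 5.8% |
| 70/20/10 | 1.40 | 0.440 | 1.78 | 0.04% | 5.6% |
| 60/25/10/5 | 1.60 | 0.740 | 1.47 | 0.34% | 5.5% |
| 50/25/15/10 | 1.85 | 1.027 | 1.34 | 0.72% | 5.1% |
| 40/25/15/10/5/5 | 2.30 | 2.110 | 1.04 | 3.96% | 5.3% |

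**Where it vanishes or reverses.** For a geometric count with first-attempt share p the factor is √(p/(1−p)): 2.0 at 80%, 1.22 at 60%, 1.0 at 50% and 0.82 at 40%. A long tail has the same effect. With 70/15/5% at 1–3 attempts, 5% at 5 and 5% at 8, the mean is 1.80, the variance 2.96 and the factor √(1.80/2.96) = 0.78. The Poisson interval is then too narrow, and the simulated type I error is about 12%.

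**Power for a modest difference.** Take 75/15/10% against 90/8/2% at 68 per arm.
- Means are 1.35 and 1.12, variances 0.4275 and 0.1456, and the log ratio is ln(1.35/1.12) = 0.187.
- Poisson SE = √(1/91.8 + 1/76.16) = 0.155.
- True SE = √(0.4275/(68 × 1.35²) + 0.1456/(68 × 1.12²)) = 0.0718.
- Poisson test: it rejects above 1.96 × 0.155 = 0.304, so power is P(Z > (0.304 − 0.187)/0.0718) = P(Z > 1.63), about 5%.
- Robust test: P(Z > 1.96 − 0.187/0.0718) = P(Z > −0.64), about 74%.

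Simulation gives the same two figures.

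**Power over other differences** (65 per arm, simulated, unadjusted):

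| Means | Poisson SE | Robust SE |
|---|---|---|
| 1.12 vs 1.40 | 12% | 86% |
| 1.25 vs 1.60 | 30% | 82% |
| 1.20 vs 1.60 | 47% | 91% |
| 1.40 vs 1.85 | 53% | 87% |
| 1.12 vs 1.60 | 76% | 99% |
| 1.25 vs 1.85 | 89% | 99% |
| 1.12 vs 1.85 | 99% | 100% |

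**The case against.** A reader might infer that nearly every patient has one attempt, that the interval is bound to be about twice too wide, and that the test can hardly ever reject. The documents do not support that. They give no distribution of attempts, and even the minimum of one is an inference, though a safe one. Protocol 3.4 and 3.6 describe navigated placement as accurate, which makes a high first-attempt share plausible, but neither gives a rate. Excluding zero rules out an exact Poisson distribution; it does not fix the size or even the direction of the standard-error problem, as the geometric and long-tail cases show. Large differences would also still be detected.

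The second argument is that the plan already allows another model when assumptions fail and requires deviations to be listed and justified, so the analysis is not locked into a wrong standard error. That is right, and the figures above apply only if the model is used as written. But the clause names no dispersion check, no threshold and no replacement. It leaves the choice until the data are seen, and it does not reach protocol 11.4.5. A misfit that can be foreseen from the nature of the outcome is better settled now.

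Third, the Poisson point estimate remains a valid mean ratio, and outcomes are also summarised descriptively by arm. That stands: the fault is confined to the interval and the test.

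**Conclusion.** The point holds as a pre-specification gap whose size is conditional. If about 70–85% of patients need one attempt and the tail is short, the model-based interval is about 1.8–2.2 times too wide; over 50–90% single attempts the factor is about 1.3–2.8. In those cases modest differences would often be missed (about 5% power instead of 74% in the worked example), while mean differences of about 0.5–0.7 would usually be found, with 76–99% power. With widely spread attempts the error disappears, and with a long tail the interval becomes too narrow.

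All these figures rest on assumed distributions and unadjusted models; the covariates planned in SAP 6.3.1.2 could shift them somewhat. Only this secondary and safety outcome is affected. The sample size and the primary conclusion are not.

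**What to change.** In SAP 6.3.1.2 and protocol 11.4.3 and 11.4.5, keep the log-link mean ratio and specify robust (sandwich) standard errors, or quasi-Poisson with estimated dispersion, as the planned analysis of puncture attempts. This replaces the open fallback for this outcome and corrects the interval whichever way the dispersion turns out. Report the proportion with one versus more than one attempt by arm beside it.

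The cost is a phrase in each section and a small change to the R code; no new data are needed and the mean-ratio estimate does not change. The downside is small: at 65 per arm the robust test ran slightly above nominal, at about 5.1–6.0%.
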